## Methods/design

### Study design

This is a prospective, multicenter, randomized clinical trial that should demonstrate the non-inferiority of the BuMA Supreme stent compared with the Xience stent on neointimal healing response evaluated by optical coherence tomography (OCT). In the current trial, the following devices will be used: BuMA Supreme stent – Biodegradable Polymer SES Coated Coronary Stent System manufactured by SINO Medical Sciences Technology Inc. and the Xience V/Prime/Xpedition stent – Durable Polymer everolimus-eluting Stent System manufactured by Abbott Company. A full range of commercially available guiding catheters, balloon catheters, and guidewires will be readily available.

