7. The patient and the patient’s physician agree to the follow-up visits including angiographic follow-up and OCT controls at 1 or 2 month	
8. Written informed consent provided	
Exclusion criteria	
1. Left ventricular ejection fraction (LVEF) < 30%	
2. Patients expected not to comply with 1-month DAPT	
3. Chronic total occlusion (TIMI 0), left main lesion, intervention-required three-vessel lesions, branch vessel diameter ≥ 2.5 mm and bypass lesion	
4. Patients requiring a planned-staged PCI procedure more than 1 week after the index procedure	
5. Procedure planned to require non-study stents, or stand-alone POBA or stand-alone atherectomy	
6. Severe tortuous, calcified or angulated coronary anatomy of the study vessel that in the opinion of the investigator would result in suboptimal imaging or excessive risk of complication from placement of an OCT catheter	

*CAD* coronary artery disease, *DAPT* dual anti-platelet therapy, *OCT* optical coherence tomography *NSAID* non-steroidal anti-inflammatory drug, *PCI* percutaneous coronary intervention, *POBA* plain old balloon angioplasty

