### Study endpoints and clinical follow-up

The primary endpoint is the stent-strut neointimal coverage rate (%) by OCT assessment at 1 month and 2 months, respectively. Secondary OCT endpoints include neointima hyperplasia area/volume, neointimal hyperplasia thickness and the stent-strut malapposition at 1 or 2 months’ follow-up, respectively. Secondary angiographic endpoints include LLL, restenosis rate of in-stent/in-segment at 1 or 2 months’ follow-up, respectively. Secondary clinical endpoints include device/lesion/clinical success rate, device-oriented composite endpoints and its individual components, other serious adverse (MI, TLR and stent thrombosis) and bleeding events at 1 or 2, 3, 6 months, 1 year and 2 years.

Target lesion failure was defined as the composite of cardiac death, target vessel myocardial infarction (MI), and ischemia-driven TLR. MI was adjudicated according to the third universal definition of MI [10]. Stent thrombosis (definite and probable) was defined according to the Academic Research Consortium (ARC) classification. All clinical events were adjudicated by an independent Clinical Events Committee (CEC). Device success was defined as attainment of < 30% residual stenosis of the target lesion by visual assessment. Lesion success was defined as attainment of < 30% residual stenosis, TIMI 3 flow, and no residual dissection or thrombosis of the target lesion using any percutaneous method. Clinical success was defined as attainment of lesion success of the target lesion and no in-hospital major adverse cardiac event.

Angiography and OCT investigations are conducted at 1 or 2 months post PCI. Clinical follow-up visits or telephone follow-up will be conducted at the first, second, third, sixth month, or 1 to 2 years post PCI.

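### Device success is defined without reference to the assigned stent, so a lesion rescued with a different stent would count, as written, as a success of the arm whose stent failed

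*Protocol article*

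**What the plan says.** All three definitions stand together in the protocol article, section Study endpoints and clinical follow-up.

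- Device success begins "Device success was defined as attainment of", gives the cut-off of less than 30%, and continues "residual stenosis of the target lesion by visual assessment. Lesion success was defined as attainment of". Its only conditions are the cut-off and the visual reading.
- Lesion success uses the same cut-off and adds "TIMI 3 flow, and no residual dissection or thrombosis of the target lesion using any percutaneous method".
- Clinical success is lesion success without an in-hospital major adverse cardiac event.

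The same section lists these rates as secondary endpoints: "Secondary clinical endpoints include device/lesion/clinical success rate". Elsewhere in the article:

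- Table 1, exclusion criterion 5, removes a "Procedure planned to require non-study stents, or stand-alone POBA or stand-alone atherectomy". It concerns what is planned, not what happens unplanned during the procedure.
- The Study design section says: "A full range of commercially available guiding catheters, balloon catheters, and guidewires will be readily available". This covers balloons but is silent on other stents.
- The Statistical analysis section compares categorical variables by chi-square or Fisher's exact test and takes the individual as the unit of analysis.

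No other part of the article ties device success to the allocated stent.

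**The concern.** A reader expects a rate called device success, compared between two randomised stents, to depend on whether the allocated stent did the job. The written rule depends only on the state of the lesion at the end, whatever achieved it. The cases that should distinguish device success from lesion success are those where the allocated stent failed and something else repaired the lesion. The definition credits those cases to the allocated stent.

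At stake is the interpretation of one secondary endpoint. If rescue occurs, the reported rate overstates how often the allocated stent succeeded. If rescue is more frequent in one arm, part or all of that difference disappears from the table.

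**Working it through.** The article states no figure for this endpoint, so there is none to reproduce. The check is one of logic, followed by the weight of a single case.

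**1. Nesting.** For one target lesion let S = residual stenosis below 30%, T = TIMI 3 flow, and N = no residual dissection or thrombosis.

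- Device success as written = S.
- Lesion success = S and T and N, by any percutaneous method.

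If S is the same reading in both, lesion success implies device success, and the device rate cannot fall below the lesion rate. The condition matters: the article specifies visual assessment for device success and names no method for lesion success, while OCT and QCA evaluation provides for core-laboratory angiographic measurement. With two different readings the nesting need not hold.

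**2. Classification of a rescued lesion.** Suppose the allocated stent cannot be placed and a non-assigned stent brings the lesion below 30%.

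| Rule | Device success |
|---|---|
| As written | yes, since S holds |
| Assigned stent type only | no |

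Without rescue the two rules agree. Exclusion criterion 5 does not rule such a case out, because it reaches only what was planned.

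**3. Weight of one case.** There are 80 patients in two cohorts of 40, each split 1:1: 20 per arm within a cohort, 40 per arm overall.

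- Per patient, overall: 1/40 = 2.5 points.
- Per patient, within a cohort: 1/20 = 5 points.
- Per lesion: Table 1 allows up to two lesions per patient, so an arm has 40 to 80 lesions, and one lesion weighs 1/80 = 1.25 to 1/40 = 2.5 points.

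These are the weights of one reclassified case, not estimates of an effect.

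**4. Illustration with assumed rates.** The documents give neither a failure rate nor a rescue rate. Assume the allocated stent fails in a fraction f of lesions, rescue reaches the cut-off in a fraction r of those (the same in both arms), and all other lesions reach it.

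- As written: success = 1 − f(1 − r); absolute difference between arms = |f₁ − f₂|(1 − r).
- Assigned stent only: success = 1 − f; absolute difference = |f₁ − f₂|.

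| Assumed f₁ vs f₂ | r | As written | Difference | Assigned stent only | Difference |
|---|---|---|---|---|---|
| 2% vs 2% | 0.9 to 1.0 | 99.8–100% in both | 0 | 98% in both | 0 |
| 10% vs 2% | 0.9 to 1.0 | 99.0–100% vs 99.8–100% | 0 to 0.8 points | 90% vs 98% | 8 points |
| 20% vs 2% | 0.9 to 1.0 | 98.0–100% vs 99.8–100% | 0 to 1.8 points | 80% vs 98% | 18 points |

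The first row shows that with equal failure rates the level is overstated but the comparison is not distorted. The other rows show the mechanism only; nothing in the article suggests rates of that size.

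**The case against.** **The intent can be read from the contrast.** The any-method clause appears in lesion success only, which, with the label, suggests that device success was meant to be confined to the study stent. That is a fair reading, but the restricting words are absent and a derivation programmed from the text would miscount. A reader might go further and infer that the trial will in fact score every rescue as a success. The article does not show that; it gives no explicit rule for a switch of stent.

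**The article is condensed.** The full protocol may carry the missing phrase. This cannot be excluded. Still, the article gives a definition that reads as complete, and what it states lacks the condition.

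**Rescue may be rare.** Table 1 excludes chronic total occlusion, left main lesions and anatomy so tortuous, calcified or angulated that imaging or the OCT catheter would be a concern. It also limits vessel diameter to 2.5–4.0 mm and lesion length to 40 mm. This stands: the number of affected cases may be small or zero.

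**Tempting overstatements.** A reader might conclude that the endpoint cannot measure device performance at all. It can wherever no rescue occurs. A reader might also conclude that the arms are necessarily pulled together. That needs both rescue and unequal failure rates, and neither is documented. Nor is a per-stent denominator built on the planned 1.5 stents per patient appropriate: success is defined per lesion and analysed per individual.

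**Conclusion.** The point holds in a limited form. As written, device success carries no device condition, so a lesion rescued with a non-assigned stent meets it. On a common stenosis reading, it is simply a weaker version of lesion success. Each rescued patient shifts the rate by 2.5 points in an arm of 40, or 5 points in a cohort arm of 20, relative to a rule that counts the assigned stent only. This takes the patient as the unit and one rescued lesion as enough to make that patient a device failure. How many such patients there will be is unknown.

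A reader might infer that the trial's main conclusion is affected. It is not: strut coverage by OCT, the margins and the sample size do not use this definition. Severity is minor: a secondary endpoint whose wording should be repaired.

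**What to change.** Define device success as residual stenosis of the target lesion below 30% by visual assessment, attained with the assigned study stent type only. State that additional stents of the assigned type and balloon pre- or post-dilatation are compatible with success, since lesions up to 40 mm and an average of 1.5 stents per patient are expected. Score use of a non-assigned stent in the target lesion as device failure. Keep the any-method clause for lesion success alone, and state there whether the stenosis is read visually or by the core laboratory.

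Confirm that the case report form records the stent actually implanted. The Randomization section asks the investigator to record the stent information that goes with the allocation; it does not say that the implanted stent is captured.

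This changes how outcomes are counted, not how patients are treated. It needs no extra patients or visits. The cost is a phrase in the definition, the matching derivation, possibly one form field, and a reported device success rate that may be slightly lower.

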### Sample size of clinical trials

The study’s primary endpoint was stent-strut neointimal coverage rate (%) by OCT assessment at the first or second month. Using a two-sided α of 0.05, 20 subjects were enrolled in each group. It was assumed that 1.5 stents would be implanted in each patient with 200 stent struts (20 mm length) for each stent. Regarding a 20% drop-out rate, 4800 stent struts were estimated to be tested. Assuming a neointimal coverage rate for both the BuMA and Xience stents of 70%, and a non-inferior margin of 3.6% at the first month, stent struts would have at least 97% power to detect that the Supreme group show non-inferiority to that of the Xience group. Assuming a neointimal coverage rate for both BuMA and Xience stents of 85%, and a non-inferior margin of 2.4% at the second month, stent struts would have at least 91% power to detect that the Supreme group shows non-inferiority to that of the Xience group. Since a competition mechanism is introduced into this multicenter study, no single center will enroll more than 40% of the patients.

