### Patient enrollment

Eighty coronary artery disease (CAD) patients with a high bleeding risk will be included from eight centers, the major inclusion and exclusion criteria are summarized in Table 1. Patients will be randomized into two cohorts using a 1:1 ratio, 40 patients will be assigned into a first-month OCT group. The other 40 patients will be assigned into a second-month OCT group. The patients in each cohort will be randomized again into two groups in a 1:1 ratio, either receiving the BuMA Supreme stent or the Xience stent. The process of patient recruitment, enrollment and randomization is summarized in Figs. 1 and 2 shows the Standard Protocol items: Recommendations for Interventional Trials (SPIRIT) Figure for the trial.

**Table 1 Tab1:** Major inclusion and exclusion criteria

Inclusion criteria	
1. The age of patients is between18 and 85 years	
2. Symptoms and evidence of myocardial ischemia without raised troponin (e.g., stable or unstable angina, silent ischemia demonstrated by positive territorial functional study)	
3. CAD patients with a high risk of bleeding. Any one or more situation listed below can be considered the patient with high bleeding risk by the investigator [6]: a) Adjunctive oral anticoagulation treatment planned to continue after PCI b) Baseline Hb < 11 g/dl (or anemia requiring transfusion during the prior 4 weeks) c) Any prior intra-cerebral bleed at any time d) Any stroke during the past year e) Hospital admission for bleeding during the prior 12 months f) Non-skin cancer diagnosed or treated ≤ 3 years g) Planned daily NSAID or steroids for ≥ 30 days after PCI h) Planned major surgery (within 1 year) i) Renal failure (calculated creatinine clearance < 60 ml/min) j) Thrombocytopenia (< 100,000/mm^3^) k) Severe chronic liver disease (variceal hemorrhage, ascites, hepatic encephalopathy or jaundice) l) Patient with previous history of gastrointestinal bleeding m) Patient meets the following 2 or more factors: “aged female,” “diabetes,” “uncontrolled high blood pressure,” “heart failure”	
4. The patient has a planned intervention of up to two de novo lesions in different epicardial vessels	
5. Lesion(s) must have a visually estimated diameter stenosis of ≥ 70% and < 100%	
6. Reference vessel diameter (RVD) must be visually estimated ≥ 2.5 and ≤ 4.0 mm, and the lesion length must be no more than 40 mm	

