### Statistical analysis

Continuous variables will be described using means and standard deviations or median and range in the case of asymmetric data distribution. Categorical variables will be presented as numbers and frequencies, and comparisons will be made using the chi-square test or Fisher’s exact test as appropriate. All time-to-event outcomes will be summarized using Kaplan-Meier survival estimates and compared among treatment groups using log-rank tests. An array of prespecified and exploratory subgroup analyses of the primary and major secondary endpoints will be performed. Statistical significance will be considered at *P* < 0.05. A statistical package (SPSS 16.0) will be used for analysis. The individual will be considered as a unit of analysis.

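### The 97% and 91% powers hold only if 4800 struts per arm are independent; they sit in about 16 patients per arm, and the plan names the individual as the unit of analysis

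*Protocol article*

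**What the plan says.** The Sample size section of the protocol article builds its case from struts. It starts from patients: "Using a two-sided α of 0.05, 20 subjects were enrolled in each group". It then converts to struts: "It was assumed that 1.5 stents would be implanted in each patient with 200 stent struts (20 mm length) for each stent", and "Regarding a 20% drop-out rate, 4800 stent struts were estimated to be tested". For month 1 it assumes 70% coverage with both stents and a margin of 3.6 points, and concludes that "stent struts would have at least 97% power to detect that the Supreme group show non-inferiority to that of the Xience group". For month 2 it assumes 85% coverage and a margin of 2.4 points, and says that "stent struts would have at least 91% power to detect" non-inferiority. It states no ICC, design effect or between-patient SD.

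The unit of randomisation is the patient (Patient enrollment: "The patients in each cohort will be randomized again into two groups in a 1:1 ratio"). The Statistical analysis section ends with "The individual will be considered as a unit of analysis". Nothing in the article links that sentence to the strut-based power.

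**The concern.** Struts in one patient share a vessel, a lesion, an implantation and a healing response, so 300 struts from one patient carry less information than 300 struts from 300 patients. The article's own Discussion reports that coverage was delayed in patients with small vessels, complex lesions, certain plaque types or diabetes. The eligibility criteria admit a spread of these: reference diameters from 2.5 to 4.0 mm, lesions up to 40 mm, and diabetes as one of the bleeding-risk factors.

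The primary non-inferiority comparison is at stake at both time points. Analysed with the individual as unit, it has less power than stated. Analysed strut by strut to match the power statement, its confidence interval is too narrow and the non-inferiority test exceeds its nominal error. The authors want the result to inform shorter dual antiplatelet therapy, so either problem matters to readers.

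**Working it through.** **Inputs from the article.** 20 patients per arm in each cohort; 1.5 stents per patient; 200 struts per stent; 20% drop-out; two-sided α 0.05, so 0.025 one-sided; coverage p = 0.70 with margin 0.036 (month 1) and p = 0.85 with margin 0.024 (month 2); true difference 0.

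**Step 1: the strut count.** 20 × 1.5 × 200 × 0.8 = 4800. The article does not say per arm, but 20 is the number in one arm, so this is the count for one arm: 16 patients × 300 struts.

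**Step 2: reproduce the stated powers.** Power = Φ(margin / SE − 1.96), with SE = √(2p(1−p)/n).
- Month 1, n = 4800: SE = √(2 × 0.7 × 0.3 / 4800) = 0.00935; Φ(0.036/0.00935 − 1.96) = 97.05%.
- Month 2, n = 4800: SE = √(2 × 0.85 × 0.15 / 4800) = 0.00729; Φ(0.024/0.00729 − 1.96) = 90.87%.
- If 4800 were the total over both arms (n = 2400), the results would be 77.7% and 64.4%.

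Both stated figures therefore come from 4800 independent struts per arm.

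**Step 3: what this implies for patients.** With 16 patients per arm and a t-test on per-patient coverage (30 df), the stated powers need an SD of observed per-patient percentages of 2.56 points (month 1) and 1.99 points (month 2). Binomial sampling of 300 struts alone gives √(0.7 × 0.3 / 300) = 2.65 points and √(0.85 × 0.15 / 300) = 2.06 points. All the permitted variation is used up before any true difference between patients enters.

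**Step 4: power with clustering.** The documents give no ICC, so the values below are assumptions. Design effect = 1 + 299 × ICC; SD of observed per-patient coverage = √(p(1−p) × design effect / 300); power from the noncentral t; expected 95% CI half-width = t × SD × √(2/n). Each pair is month 1 / month 2.

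| ICC | Design effect | Observed SD (points) | Power, 16 per arm | Half-width, 16 per arm (points) | Power, 20 per arm |
|---|---|---|---|---|---|
| 0.001 | 1.30 | 3.0 / 2.4 | 90% / 80% | 2.2 / 1.7 | 96% / 88% |
| 0.005 | 2.50 | 4.2 / 3.3 | 66% / 52% | 3.0 / 2.4 | 76% / 62% |
| 0.01 | 3.99 | 5.3 / 4.1 | 46% / 36% | 3.8 / 3.0 | 56% / 44% |
| 0.05 | 15.95 | 10.6 / 8.2 | 15% / 12% | 7.6 / 5.9 | 18% / 14% |
| 0.10 | 30.90 | 14.7 / 11.5 | 10% / 8% | 10.6 / 8.3 | 11% / 9% |

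The SD column includes the binomial noise. The true between-patient SD is √(ICC × p(1−p)); at ICC 0.01 that is 4.6 / 3.6 points.

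**Step 5: error if struts are analysed as independent.** With the true difference at the margin, the one-sided error is Φ(−1.96 / √(design effect)): about 4% at ICC 0.001, 16% at 0.01, 31% at 0.05 and 36% at 0.10, against a nominal 2.5%.

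**The case against.** The strongest reply is that the sentence on the individual as unit is generic. It closes a condensed section that names no primary non-inferiority test, and a strut-level model clustered on the patient would be compatible with it; an analysis plan that is not shown may specify one. This is a fair limit. The article does not commit to a t-test on patient means, and the t-test here serves only to size the problem. But no choice of model makes 97% and 91% true for about 16 patients per arm unless the ICC is close to zero, and those figures stand in the article itself.

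A reader might infer that the trial has little chance of showing non-inferiority. The documents do not support that as a fact, because they give no ICC or between-patient SD. At ICC 0.001 the power is still 90% / 80%, and at 0.005 it is 66% / 52%. Against this, an ICC of 0.01 corresponds to quite homogeneous patients (true SD 4.6 / 3.6 points) and already brings power to 46% / 36%.

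A reader might also infer that a strut-level analysis would make a false non-inferiority claim likely. Errors of 16% to 36% for ICCs from 0.01 to 0.10 are badly inflated, but all are below one half, and nothing in the article says that such an analysis will be run.

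Finally, the arithmetic of the power calculation is correct on its own terms. The fault lies in the independence assumption and in the mismatch of units.

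**Conclusion.** The 97% and 91% power statements are wrong as written. They assume that patients do not differ in true coverage, which conflicts with the stated unit of analysis and with the article's own account of what delays coverage. How much power is lost is unknown, because it depends on an ICC that the documents do not give. Over assumed ICCs from 0.001 to 0.10, power with 16 patients per arm runs from 90% down to 10% at month 1 and from 80% down to 8% at month 2. These figures rest on 300 struts per patient, equal true coverage, one-sided 2.5% and a patient-level t-test. Full retention of 20 per arm helps only modestly (56% / 44% at ICC 0.01). That 4800 is a per-arm count is inferred, but the strut arithmetic and the reproduction of both powers support it.

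**What to change.** 1. Withdraw the 97% and 91% figures.
2. Restate power and expected 95% CI width for 16 and for 20 patients per arm, over a stated range of ICC or between-patient SD, saying whether any SD includes the binomial noise.
3. Align the primary non-inferiority analysis with the individual as unit: either mean per-patient percentage of covered struts, or a strut-level GEE or mixed model clustered on patient with a small-sample correction.
4. Add that failure to meet the margin at this size is not evidence of inferiority.

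Recasting the comparison as estimation with confidence intervals is optional. It would change the non-inferiority objective given in the Abstract and under Study design, so those sections would have to change too.

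Cost: rewording of the sample size and analysis sections, and no more patients. The stated power becomes much less favourable.
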